### Primary outcome: bone level

Because jaw was used for randomization, we extend Gilthorpe’s mixed model by inserting jaw to levels for patient, tooth, and site [38] and adjust for model complexity by using the Kenward-Roger correction [39]. To ensure hierarchical levels, tooth positions within each jaw are coded from 1 to 16 instead of from 1 to 32 on patient level. The first adjustment set consists of risk factors of periodontal disease including age, gender, and smoking [40]; and design variables including centre, jaw [41], jaw classification, and time. Because X-ray at t_0_ is assessed before differentiating treatment in groups, it is a baseline measurement which can additionally be used to increase efficiency [42]. Note also the discussion on pages 158–160 in Harrell’s textbook [43]. The syntax of the basic confirmatory model with the highest statistical power for the factor group is (Stata’s version 14):

Here, only the time points t_4_ and t_6_ are used as dependent variable (Table 2). To interpret changes after 12 and 36 months in exploratory analyses, we include t_0_ as dependent variable:

In sensitivity analyses, we allow for continuous time instead of points in time, for correlated random effects, or for random effects of other than tooth level and suspend the Kenward-Roger correction. In the second adjustment set, jaw classification is replaced by patient’s mean probing depth before randomization; in the third and fourth set, school education will be added to the first and second set, respectively.

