**Methods/design:**

The purpose of this study is to test the hypothesis that immediately loaded mini-implants show more bone loss and less success than strategic mini-implants with delayed loading. In this four-center (one university hospital, three dental practices in Germany), parallel-group, controlled clinical trial, which is cluster randomized on patient level, a total of 80 partially edentulous patients with unfavourable number and distribution of remaining abutment teeth in at least one jaw will receive supplementary min-implants to stabilize their PRDP. The mini-implant are either immediately loaded after implant placement (test group) or delayed after four months (control group). Follow-up of the patients will be performed for 36 months. The primary outcome is the radiographic bone level changes at implants. The secondary outcome is the implant success as a composite variable. Tertiary outcomes include clinical, subjective (quality of life, satisfaction, chewing ability) and dental or technical complications.

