### Interventions

Dentists of the centers with experience in dental implantology for more than ten years, who are familiar with the mini-implant system, perform the surgical and prosthetic treatment. Standard operating procedures were specified in a manual and imparted during the first calibration meeting. The first implant placement in each center was supervised by the treatment coordinator (TC) of the leading center.

Mini dental implants (MDI, 3 M ESPE, Seefeld, Germany) with lengths of 10 to 18 mm and diameters of 1.8 mm, 2.1, and 2.4 mm are used for the stabilization of PRDPs (Figs. 1 and 2). The total number of abutments per quadrant (with unfavourable distribution and number of remaining abutment teeth) will be increased to at least 3 in the maxilla or at least 2 in the mandible by the insertion of strategic MDIs (Table 1). The posterior MDI should be placed at the most posterior area of the dental arch according to the local bone volume. In the mandible, the MDIs should be located always mesial of the mental foramen. Whenever possible, the region of the canine should be occupied by an MDI (alternatively the regions of the first premolar and the lateral incisor should show abutments after intervention). If the insertion torque of one implant is < 15 Ncm due to poor bone quality the patient must be excluded from the study. Recesses for female matrices (housings) were prepared in the existing PRDP. Thereafter, a sealed envelope with the randomization detail was opened and the patient was allocated either to test group A (immediate loading/restoration) or control group B (delayed loading).

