### Randomization and blinding

The randomization was performed centrally by the trial statistician based on a sequence of computer-generated numbers with a 1:1 allocation ratio stratified by jaw (maxilla, mandible) and study center.

Due to the apparent treatment differences, it is not possible to blind the dentists, clinical investigator, and/or the participating patient. However, the two examiners of the radiographs and the statistician will be blinded.

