### Statistical methods

Because of the statistical power, we choose the continuous variable bone level to be the primary outcome measure. We differentiate confirmatory and exploratory analyses. Confirmatory analysis is related to differences between groups whereas exploratory analysis is related to the rate of change between groups (interaction between time and group), which yields low power test herein. However, we present the joint test of the factor group and the interaction between time and group. The explanations of the variables are outlined in Table 2.

**Table 2 Tab2:** Variables, measures, hypotheses, and methods of analysis

Variable	Measure, parameterization	Variable name for syntax	Level	Hypothesis	Points in time	Methods of analysis: Stata command (version 14)
1. Primary outcome						
a) Bone level	Radiographic bone levels around implants (mesial, distal, mm, continuous)	Bone level	Implant	Group A will show more bone loss than group B	(t_0_), t_4_, t_6_	Mixed model for continuous responses: mixed
2. Secondary outcome: Implant success	Modified criteria of Albrektsson (binary): composite variable on implant level	Success	Implant	Group A will show less success than group B	t_4_, t_6_	Mixed model for binary responses: melogit
a) Related to infection	Modified sulcus bleeding index (0–3 on 2 sites per implant)	SBI	Implant		t_1_, t_2_, t_3_, t_4_, t_5_, t_6_	Mixed model for ordinal responses: meologit
	Bleeding on probing (binary on 4 sites per implant)	BOP	Implant		t_1_, t_2_, t_3_, t_4_, t_5_, t_6_	Mixed model for binary responses: melogit
b) Clinical immobility	Clinical immobility of the implant (binary)	Mobility	Implant		t_1_, t_2_, t_3_, t_4_, t_5_, t_6_	Mixed model for binary responses: melogit
c) Pain	Persistent pain or discomfort (binary)	Pain	Implant		t_1_, t_2_, t_3_, t_4_, t_5_, t_6_	Mixed model for binary responses: melogit
d) Radiolucency	Evidence of peri-implant radiolucency (binary)	XLucency	Implant		t_4_, t_6_	Mixed model for binary responses: melogit
e) Survival	Implant in situ (binary)	ImplantLoss	Implant		Continuous time	Kaplan-Meier
3. Tertiary outcome						
a) Periodontal and periimplant conditions	Probing depths (mm, continuous on 4 sites per implant)	ProbingDepth	Implant	Group A will show higher values than group B	t_1_, t_2_, t_3_, t_4_, t_5_, t_6_	Mixed model for continuous responses: mixed

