	Probing depths (mm, continuous on 4 sites per tooth)	ProbingDepth	Tooth	Overall improvement at teeth, improvement occurred faster in group A than in group B	t_1_, t_2_, t_3_, t_4_, t_5_, t_6_	Mixed model for continuous responses: mixed
	Osstell (0–100, continuous on implant level)	Osstell	Implant	Group A will show lower values than group B until the fourth month, thereafter equalization between A and B	t_1_, t_2_, t_3_, t_4_, t_5_, t_6_	Mixed model for continuous responses: mixed
	Periotest (−8.0 - +50.0, continuous on tooth level)	Periotest	Tooth	Overall improvement at teeth, improvement occurred faster in group A than in group B	t_1_, t_2_, t_3_, t_4_, t_5_, t_6_	Mixed model for continuous responses: mixed
	Periotest (−8.0 - +50.0, continuous on implant level)	Periotest	Implant	Group A will show higher values than group B until the fourth month, thereafter equalization between A and B	t_1_, t_2_, t_3_, t_4_, t_5_, t_6_	Mixed model for continuous responses: mixed
b) Oral health related quality of life	OHIP-G14 questionnnaire (0–56, continuous)	OHIP	Patient	Overall improvement, improvement occurred faster in group A than in group B	t_1_, t_2_, t_3_, t_4_, t_5_, t_6_	Mixed model for ordinal responses: meologit
c) Patient’s satisfaction with the PRDP	Questionnnaire 8 items (Five-point Likert-scale, 8–40 continuous)	Satisfaction	Patient	Overall improvement, improvement occurred faster in group A than in group B	t_1_, t_2_, t_3_, t_4_, t_5_, t_6_	Mixed model for ordinal responses: meologit
d) Nutrition of the patients	Food frequency questionnaire (1–7)	FFQ	Patient	Overall improvement, improvement occurred faster in group A than in group B	t_1_, t_2_, t_3_, t_4_, t_5_, t_6_	Mixed model for ordinal responses: meologit
	Food avoidance questionnaire (binary)	FAQ	Patient	Overall improvement, improvement occurred faster in group A than in group B	t_1_, t_2_, t_3_, t_4_, t_5_, t_6_	Mixed model for binary responses: melogit
e) Chewing efficiency	Colour-mixing ability test with two coloured chewing gum (continuous)	Chewing	Patient	Overall improvement, improvement occurred faster in group A than in group B	t_1_, t_2_, t_3_, t_4_, t_5_, t_6_	Mixed model for ordinal responses: meologit
4. Exposure						
Group	2 categories		Jaw		t_0_	
5. Time variables						
TimePoint	0-6 for outcomes				0-6 for t_0_ –t_6_	
Week	Time [weeks]		Patient		Week	
SqrtWeek	Square root of week		Patient		Root of week	
Time			Patient		Continuous	
6. Confounder						

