### Per protocol set

We define the per-protocol by the following criteria: only one study jaw per patient; minimum number of implants as indicated in Table 1; no poor general health, no bisphosphonate therapy, no mental disorder, and no drug abuse during follow-ups; X-ray examination after 36 months is available.

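### The article gives both patient and jaw as the unit that carries the randomised group, and plans implant survival with no stated allowance for clustering within patients

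*Protocol article*

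**What the plan says.** Patient as the unit:

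- The article title describes a trial randomised by patient cluster, and the abstract calls it a trial "which is cluster randomized on patient level".
- The Interventions section allocates the person once the envelope is opened ("the patient was allocated either to test group A (immediate loading/restoration) or control group B (delayed loading").
- The Sample size section counts patients: 80 in total, 40 per group.

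Jaw as the unit:

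- The section on the primary outcome justifies an added model level with "Because jaw was used for randomization".
- The exposure row of Table 2 reads "Group 2 categories Jaw". The same table places age, gender and centre at patient level.

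The Randomization and blinding section names jaw only as a stratum: allocation is "stratified by jaw (maxilla, mandible) and study center".

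Two-jaw patients are foreseen. Eligibility covers a prosthesis in either jaw or both, and the per-protocol set is limited by the criterion "only one study jaw per patient", which would be empty if nobody could have two.

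The survival row of Table 2 ("Implant in situ (binary") is at implant level, in continuous time, with Kaplan-Meier as the whole method. The other implant-level outcomes in the table are assigned a linear, logistic or ordinal mixed model.

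**The concern.** The level at which the group varies determines which comparisons are between patients and which are within them. Quality of life, satisfaction, nutrition and chewing are measured once per patient. If Group really were an attribute of the jaw, a patient whose two jaws fell into different arms would have no single group value for these outcomes. If Group belongs to the patient, the arm is clear, but a patient with both jaws in the study fits neither the maxilla nor the mandible stratum. Either way, a reader cannot reconstruct how such patients are handled.

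The survival point is separate. Implants in one mouth share bone quality, prosthesis, hygiene and operator, so their failures are likely to be positively correlated. The plan models this clustering for the other implant-level outcomes but says nothing about it for survival. Implant loss matters here: being in situ is the first element of the success composite.

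**Working it through.** **1. Which unit the sample size uses.** Inputs (Sample size section): difference 0.4 mm, SD 0.5 mm, two-sided alpha 0.05, power 80 %. The standardised difference is 0.4/0.5 = 0.8. A two-sample t-test needs n = 25.5, rounded up to 26 per group, with power 80.7 %. The stated 26 is reproduced. At 75 % response, 26/0.75 = 34.7, so 35 per group; the stated 40 is more generous. The calculation has one observation per patient, which fits the patient as unit.

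**2. Can one reading reconcile the passages?** Suppose the phrase about jaw and randomisation means only stratification. It then agrees with the Randomization section, and the primary-outcome section itself lists centre and jaw together as design variables. The Table 2 entry remains: under patient-level allocation with jaw as a stratum, Group would sit at patient level, like centre. So one cell stays in conflict under the kindest reading, and two places conflict under the literal one.

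**3. Survival precision.** The article gives neither a mean number of implants per patient (m) nor an intra-patient correlation (ICC). Assumptions: m = 2 or 4 (the case in Fig. 1 has 4) and ICC 0.2 to 0.5. The design effect is 1 + (m − 1) × ICC, and its square root is the factor by which an independent-implant standard error must be multiplied.

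| m | ICC | Design effect | SE factor |
|---|---|---|---|
| 2 | 0.2 | 1 + 1 × 0.2 = 1.2 | 1.10 |
| 2 | 0.5 | 1 + 1 × 0.5 = 1.5 | 1.22 |
| 4 | 0.2 | 1 + 3 × 0.2 = 1.6 | 1.26 |
| 4 | 0.5 | 1 + 3 × 0.5 = 2.5 | 1.58 |

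At a lower ICC of 0.05 the factors are about 1.02 (m = 2) and 1.07 (m = 4).

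By normal approximation, a nominal 95 % interval that ignores clustering covers 2Φ(1.96/factor) − 1. With m = 4 this is 87.9 % at ICC 0.2 and 78.5 % at ICC 0.5.

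Check by beta-binomial simulation: 40 patients per arm, 4 implants each, true survival 0.95, ICC 0.2, no censoring. The independent-implant SE is √(0.95 × 0.05/160) = 0.0172. The simulated SD of the survival estimate was 0.0219, a ratio of 1.27, in line with 1.26. The mean Greenwood SE was 0.0168.

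**4. Per-protocol model.** With one jaw per patient, patient and jaw random intercepts index the same units. In a worked example (20 patients, variances for patient, jaw, tooth, site and residual), the REML information matrix had rank 4 for 5 components, so only the sum of patient and jaw variance can be estimated. The SE of the group effect was 0.160 for every split of that sum between the two levels.

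**The case against.** Most of the text settles on the patient, jaw is named as a stratum, and the primary model carries both patient and jaw as levels, so it allows for clustering wherever the group varies. This stands: no harm to the primary bone-level comparison is shown. The Table 2 entry and the missing rule for two-jaw patients are still there to correct.

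Three stronger inferences are tempting, and the article does not support them.

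- *That patients hold scores belonging to both arms.* This needs separate allocation of a patient's jaws. No passage says it happened, and the allocation step says the opposite. The number of two-jaw patients is not given.
- *That the per-protocol model cannot be fitted meaningfully.* Only the split between patient and jaw variance is undetermined; the group effect and its SE are not affected. Nor does the article say that all levels are kept for that set, and the model syntax is absent from the text available.
- *That the survival intervals are too narrow.* No interval, variance method or group test is specified for survival, and a condensed article may leave these to the full plan. The understatement arises only if ordinary implant-level methods are used. What can be said is that survival alone among the implant-level outcomes is assigned a method that does not handle clustering by itself.

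**Conclusion.** The contradiction on the unit is in the text and should be reconciled. Its effect on results cannot be sized because the number of two-jaw patients is unknown. It may be nil if every patient was allocated once, as the title, abstract and allocation step indicate.

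For survival, the Kaplan-Meier estimate is not in question. If it is accompanied by ordinary implant-level intervals or tests, these overstate precision for any positive within-patient correlation, by the SE factors tabulated above. Those factors rest on assumed values of m and ICC and on equal numbers of implants per patient.

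The redundancy of patient and jaw levels in the per-protocol set is a matter of tidiness. The point as a whole is worth correcting before analysis, but it does not undermine the primary comparison.

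**What to change.** - State the patient as the randomised unit throughout, set Group to patient level in Table 2, and reword the primary-outcome section so that jaw is described as a stratum and a model level.
- Report how many patients had two study jaws, and the arm and stratum actually used for each. Recruitment and implant placement are finished, so this is disclosure and cannot alter allocation.
- If any patient's jaws were allocated separately, say so and examine the effect in a sensitivity analysis. Dropping such patients by default would be a post-randomisation exclusion.
- Give survival intervals and any group comparison a patient-clustered variance: bootstrap by patient, robust variance, or shared frailty on patient.
- In the per-protocol set, use one random level for patient and jaw.

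Cost: a few lines of wording, small changes to syntax, and slightly wider survival intervals. No new data and no change to sample size are needed.

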### Secondary outcomes

To avoid false positive conclusions, we state a priority ordering in advance [44] based on information on scale (continuous/ordinal/binary), number of time points, level (site/tooth/jaw/patient), and expected number of events (see Table 2).

For six time points, we allow for nonlinear change. The nonlinear change is modelled by taking the square root of time [45] because we expect a higher rate of change in the first weeks. The confirmatory and the exploratory SBI model:

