**Fig. 4 Fig4:**
[figure not shown]
Organization chart of the trial

Tertiary outcomes arePeriodontal and peri-implant conditions (probing depths, bleeding on probing (BOP), modified plaque index, modified sulcus bleeding index (mod. SBI), tooth and implant mobility measured by Periotest and Osstell)Oral health related quality of life (measure: short German version of the oral health impact profile (OHIP-G14) [33] and Patient’s satisfaction with the PRDP (Likert scale: totally satisfied - not at all satisfied) [34]Food frequency and avoidance questionnaire will be completed by the patients to evaluate the nutrition of the patients [35]Chewing efficiency will be quantified with colour-mixing ability test using a two coloured chewing gum (optoelectronical.evaluation of the ratio of unmixed colour pixels to the total pixel number in a fixed size template) [36]Dental and prosthetic complications: tooth loss, caries, endodontic treatment, implant- or tooth fracture, prosthesis fracture, loss of retention, housing detachments, loss of O-rings.

We hypothesized that after the placement of MDIs there will be significant improvements only in group A and not in group B at the baseline and at the 4- month follow-up examination. After the pick-up of the housings in group B there will be also significant improvements for patients of this group.

Examinations for all secondary outcomes are scheduled before implant placement (pre-treatment, exclusively outcomes No.1- 4), 14 days after implant placement (baseline) and 4, 12, 24 and 36 months after implant placement (Fig. 4). In addition, patients whose housings are picked-up after 4 months will be examined 14 days after the pick-up. A trained examiner of the leading treatment center not involved in the treatment of participants will perform all examinations. Additionally, a second examiner will survey the bone levels at implants on the radiographs.

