### Tertiary outcomes

See Table 2 for priority ordering. We allow for nonlinear change as described above. If possible we adjust for values before treatment [40, 43]. The confirmatory and the exploratory model of periotest for teeth:

For tertiary outcomes other than periodontal or peri-implant conditions, we expect differences between groups before housing in group B (time points t_1_ and t_2_) but no differences after that (time points t_4_-t_6_). Thus, we present only confirmatory analyses. The model for food frequency questionnaire at time points t_1_ and t_2_:

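### For tooth probing depth and tooth Periotest, square-root time counted from placement does not suit an arm predicted to respond only after month 4, so the exploratory group × time term should not be used to judge whether group A improves faster

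*Protocol article*

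**What the plan says.** The Secondary outcomes section states that, for outcomes with six time points, nonlinear change is "modelled by taking the square root of time [45] because we expect a higher rate of change in the first weeks". The Tertiary outcomes section carries this over ("We allow for nonlinear change as described above") and announces a confirmatory and an exploratory model for tooth Periotest. Among its time variables Table 2 lists "Square root of week". It lists no variable that starts at loading. The Outcomes section schedules the examinations "14 days after implant placement (baseline) and 4, 12, 24 and 36 months after implant placement", so both arms share one time origin.

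The Interventions section leaves the recesses of group B empty for four months. After listing the tertiary outcomes, the Outcomes section predicts that "there will be significant improvements only in group A and not in group B at the baseline and at the 4- month follow-up examination", with improvement in B following pick-up. For tooth probing depth and tooth Periotest, Table 2 gives the hypothesis "Overall improvement at teeth, improvement occurred faster in group A than in group B".

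The Statistical methods section says that "exploratory analysis is related to the rate of change between groups (interaction between time and group"). It calls this a low-power test and adds a joint test of group and interaction.

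**The concern.** The reason given for the square root is that change is quickest in the first weeks after placement. Under the plan's own prediction that describes A. B is expected to stay flat for about 17 weeks and then respond, at a point where the square-root curve has already flattened.

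The modelled responses begin at t1 (day 14), with the pre-treatment value as a covariate where possible. A's gain is therefore partly or mostly present early in the modelled window, while all of B's gain falls later within it. A single slope per arm can then be steeper in B precisely because A responded first. The interaction is the analysis that the plan ties to rate of change. A reader who takes its sign as the answer to whether A improves faster could report the opposite of what happened, for the two tooth outcomes that carry this hypothesis and keep a rate-of-change model.

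**Working it through.** The plan gives no figure for this point, so there is none to reproduce. The check codes the plan's own prediction and fits the described time function to it.

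**Inputs from the article.** Visits at 0.5, 4, 4.5, 12, 24 and 36 months (Table 2 footnote), counted from placement; B unloaded until month 4. With 52.18/12 weeks per month, the weeks are 2.17, 17.39, 19.57, 52.18, 104.36 and 156.54. Their square roots are 1.474, 4.170, 4.423, 7.224, 10.216 and 12.512, with mean 6.670 and sum of squared deviations 85.31.

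**Assumptions.** Improvement is a fraction of the full gain (a fall in probing depth or Periotest counts as positive). A follows 1 − exp(−t/τ); B follows the same curve started at month 4. The article gives no τ, so it is ranged.

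**Worked case, τ = 8 weeks.**
- A at the six visits: 0.238, 0.886, 0.913, 0.998, 1.000, 1.000. Slope = 4.438/85.31 = 0.052 per square-root week.
- B at the six visits: 0, 0, 0.238, 0.987, 1.000, 1.000. Slope = 9.400/85.31 = 0.110.
- Fitted at month 4: A 0.709, B 0.262, difference 0.447. True: A = 1 − exp(−17.39/8) = 0.886, B = 0, difference 0.886.

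**One square-root slope per arm, all six visits.**

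| τ (weeks) | slope A | slope B | B/A | fitted A−B, month 4 | true A−B, month 4 | fitted B, month 4 (true 0) |
|---|---|---|---|---|---|---|
| 2 | 0.021 | 0.099 | 4.8 | 0.53 | 1.00 | 0.36 |
| 4.3 | 0.038 | 0.106 | 2.8 | 0.50 | 0.98 | 0.30 |
| 8 | 0.052 | 0.110 | 2.1 | 0.45 | 0.89 | 0.26 |
| 13 | 0.065 | 0.112 | 1.7 | 0.38 | 0.74 | 0.23 |
| 26 | 0.082 | 0.111 | 1.4 | 0.27 | 0.49 | 0.19 |
| 52 | 0.086 | 0.100 | 1.2 | 0.17 | 0.28 | 0.13 |
| 156 | 0.0585 | 0.0591 | 1.01 | 0.07 | 0.11 | 0.06 |

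B is steeper at every τ tried from an immediate step to 36 months. This also holds if A has no t3 visit, which is scheduled only for patients with pick-up at month 4. Leaving t3 out of both arms gives 0.060 against 0.108 at τ = 8 weeks, with a fitted month-4 difference of 0.37. At τ = 156 weeks the two slopes are then practically equal (0.057 each).

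**Linear week term added to the square root, six visits.** Square-root coefficients, A against B:
- τ = 2: 0.121 against 0.259
- τ = 4.3: 0.214 against 0.233
- τ = 8: 0.257 against 0.215
- τ = 13: 0.260 against 0.192

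The reversal remains only at τ of about 4 weeks or less. The month-4 misfit stays. At τ = 8 the fitted difference is 0.49 (0.41 without t3) against a true 0.89, and B is credited with 0.30 of its gain before loading (0.35 without t3).

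**Sampling noise, illustrative.** A random-intercept simulation assumed 30 patients per arm, a full gain of 0.5, and between- and within-patient SDs of 0.7 each, with 150 runs per τ and one square-root slope per arm. The interaction pointed to B in 99%, 98%, 89%, 81% and 59% of runs for τ = 0, 1, 3, 6 and 12 months. It was significantly in A's favour in none of the runs up to 6 months and in 0.7% at 12 months.

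**The case against.** The strongest objection is that the model code is not visible. The text breaks off where the syntax should stand, and Table 2 lists a time-point variable, week, square root of week and continuous time. Nothing shows that the square root enters alone, and with a linear week term the reversal largely goes away. This stands: the sign reversal is conditional on the model form. The month-4 misfit is less dependent on it, since it appears under both forms tried.

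Second, the scope is narrow. The sentence that sets square-root time concerns the secondary outcomes, whose component rows in Table 2 carry no hypothesis of faster improvement in A. For quality of life, satisfaction, nutrition and chewing, the Tertiary outcomes section expects differences only at t1 and t2, presents no exploratory model, and models the food frequency questionnaire at those two visits. This also stands. A reader might infer that every rate-of-change hypothesis in the trial is affected; the article does not support that.

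Third, the interaction is exploratory, and nowhere does the plan say that its sign decides which arm is faster. A group difference in A's favour with B catching up is what the hypothesis predicts. That is correct, but the plan links the interaction to rate of change and names no other contrast for this hypothesis in the tooth outcomes. The joint test has no direction.

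Fourth, one might infer that the model shrinks the early A−B difference throughout. It does not. At t1 and τ = 8 weeks, the single-slope fit gives 0.60 against a true 0.24, so it inflates the difference there; the shrinkage is at month 4.

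Finally, τ has no source in the article, and part of A has a soft reline until month 4, so A's response may be less uniform than assumed.

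**Conclusion.** The point holds for the exploratory time-course models of tooth probing depth and tooth Periotest. The stated rationale for square-root time fits one arm only, by the plan's own prediction. With a single square-root slope per arm, a true hypothesis is expected to give a steeper slope in B: about twofold at τ = 8 weeks, and close to equal for slow responses. With a linear week term the square-root coefficient reverses only for fast responses, but the model still shows roughly half of the true month-4 difference at τ = 8 weeks and gives B improvement before its implants are loaded.

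This rests on three assumptions: the same response curve in both arms shifted by four months, time counted from placement, and the no-improvement-in-B prediction applying to the tooth outcomes as listed.

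It would go too far to conclude that the trial's time-course question must be answered wrongly or that its main conclusions are at risk. The primary bone-level analysis does not use this model. The confirmatory group effect still reflects A's advantage (average A−B over the six visits 0.33 of the full gain for an immediate response, 0.30 at τ = 8 weeks), and the joint test remains available. The harm is a misread exploratory interaction and a distorted month-4 picture for two outcomes.

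**What to change.** In the exploratory models for tooth probing depth and tooth Periotest, replace square-root time by visit as a category with a group × visit term. Test faster improvement in A as the adjusted A−B difference at t1 and t2 that disappears at t4 to t6, reported as estimates with confidence intervals. This is the pattern that the Tertiary outcomes section already expects for the other tertiary outcomes. Leave t3 out of the contrast, because in A only patients with pick-up at month 4 attend it. State that the hypothesis is not read from the sign of the group × square-root-time term.

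The change uses scheduled visits and needs no new data. It costs a few degrees of freedom and the smooth-curve summary.
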